### Psychosocial measures

Several physical activity-related psychosocial measures will be collected. Enjoyment of physical activity (16 items) [39], motivation (20 items) [40] and confidence to take part in physical activity (8 items) [41], social support for physical activity from family (3 items) and friends (5 items) [42] and attitudes towards being active (14 items) [43] will be assessed. All of these questionnaires include a five point likert scale, apart from social support (four point). Questions on global self-esteem (6 items), physical self-worth (5 items) and body attractiveness (7 items) will be adapted from the physical self-perception profile questionnaire [44]. Participants will also be asked about their intentions to be active for at least 60 min every day during the next month using three items on a 7-point likert scale (from very unlikely to very likely) adapted from Hagger and colleagues [45]. Perceived autonomy support during physical education will be assessed with six items from the adapted version of the Sport Climate Questionnaire [46]. Responses will be reported on a 7-point likert scale from strongly disagree to strongly agree.

### Negative health behaviours

Data on smoking and alcohol will be assessed using questions from the Health Survey for England [47]. Participants will be asked if they have ever tried smoking a cigarette (yes/no) and if they have, how often have they smoked as well as if they have ever drank an alcoholic drink (yes/no) and how often.

### School environment measures

Participant’s perceptions of the school physical activity environment will be assessed using a slightly modified version of the Questionnaire Assessing School Physical Activity Environment (Q-SPACE-R) [48]. The Q-SPACE-R has 16 items, eight assess the school’s physical, physical activity environment (i.e., equipment, facility quality and programming) and eight assess the school’s social physical activity environment. Answers are given on a five point likert scale from strongly agree to strongly disagree.

Lead PE teachers will complete a school characteristics questionnaire containing the following questions: 1) availability, opportunities and access to physical activity and recreation facilities; physical activity, PE and sport policies and practices; and the structure of PE classes and clubs (i.e. male and female mixed or one sex only). These questions were adapted from the ISCOLE school administrator questionnaire [49]; 2) an inventory on the types of physical activities offered by the school. These questions were adapted from the PE and Sport Survey [50]; 3) an inventory of other programmes that are offered by the school to girls in Key Stage 3; and 4) number of teachers, PE teachers and PE support staff in the school. Questions were in the format of multiple choices with free text space to allow the teachers to expand on their answers. These will be followed up with supporting questions in the process evaluation.

### Process evaluation

Process evaluation will be used to help explain any discrepancies between expected and observed outcomes, to understand the influence of context on study outcomes and to elucidate what specific components of Girls Active are deemed a success by pupils and teachers to help inform future intervention development and implementation [51]. Process evaluation will be undertaken throughout the intervention from project initiation to conclusion. We will employ a variety of techniques (e.g., observations, log books, questionnaires, interviews and focus groups with teachers and girls) to record information on recruitment, the implementation/delivery of the intervention, the extent to which the intervention reached the intended targets and the degree to which the targets engaged with ‘Girls Active’ (dose, fidelity, reach and exposure). We will also document any environmental factors that may impact on the study. This may include changes in local or national physical activity and school sport policies, contamination by other similar programmes offered, movement of any teachers from intervention to control schools and secular trends) that may have an influence on intervention effectiveness. As intervention acceptability predicts continued use of intervention strategies [52], student enjoyment and teacher acceptability will also be assessed. Details of the process evaluation components are presented in Table 1.

**Table 1 Tab1:** Outline of process evaluation

Indicators	Data sources	Timing
**Recruitment**		
Number of schools invited, number of school accepting invitation	Project records, include socio-demographic information (e.g., school size, ethnicity, SES)	Ongoing throughout project
Number of possible participants at each school, number of participants recommended or invited to attend activities, actual number who do attend each activity	School rolls, project records, attendance records	
Number who opt out	Attendance records; survey to explore reasons	
**What was delivered**		
Number of activities delivered, changes to school policy, number of peer leaders recruited, resource use, funding applied for, training conducted and attendance at training	School 'Mission Analysis' self-review and action plan, school environment questionnaire, teacher and peer mentor logs, policy review, project records for funding and training, interviews with lead teacher and peer mentors, logs from and interviews with intervention deliverers, audit of school provision	Monthly collection of logs/records, brief interviews at regular intervals throughout project, final exit interviews including review of initial 'mission analysis', end of intervention policy review and school environment questionnaire (pre-, post-)
**Description of unintended events**		
It is useful to note whether there were any unexpected side effects or outcomes from the intervention. For example, did participants take up one type of physical activity but stop doing another during the project? Unexpected outcomes do not necessarily have to be negative and there may be unanticipated positive health outcomes.	Survey with pupils, attendance logs	monthly collection of attendance, exit survey
**Participant satisfaction, acceptability and enjoyment**		
Satisfaction/dissatisfaction with the programme; likes and dislikes	Lead teacher interview; teacher focus groups; peer leaders focus groups; pupils brief exit survey to all pupils, focus groups with subset. All conducted by person independent of the intervention delivery to encourage honest opinions	Midpoint (brief) and exit
**Understanding supporting networks**		
What local and national infrastructure exists that schools/lead teachers perceive as useful to support physical activity promotion; extent to which formal or informal networks exist and are used	Interview with lead teachers of control and intervention schools	Midpoint and exit
**Sustainability**		
Whether plans have been made to continue with the intervention in some way	Interview with lead teacher	Exit interview

### Statistical analysis

This study will be analysed and reported according to the CONSORT statement for cluster RCTs. Data will be analysed on a complete case basis. The purpose of the primary analysis is to examine whether objectively measured MVPA at 14 months is higher in the intervention group than the control group. This will be examined using a linear multilevel model with MVPA as the outcome variable, levels to indicate the clustering of pupils within schools, a binary indicator for randomisation group as the explanatory variable, and terms for the stratification factors as confounders. Secondary outcomes, including those measured at other time-points, will be analysed using the same strategy with linear multilevel models used for continuous outcomes and logistic multilevel models used for categorical variables. Any changes in MVPA will be explored by extending the multilevel models to investigate whether the measured individual or school level characteristics mediate these changes. Sub-group analyses involving interaction and stratified analyses will be performed for non-active vs. active participants (defined as below or above the median MVPA level at baseline), single vs. mixed sex schools, white vs. BME participants and the degree of social deprivation based on the English indices of deprivation for the school location. These sub-group analyses will use the same models as the main analysis. Missing data will be replaced using multiple imputation methods. As a sensitivity analysis, we will repeat the analysis on both an intention to treat basis and per-protocol basis. To allow intention-to-treat analyses, missing data will be imputed using multiple imputation methods. The per-protocol analysis will only include those who were compliant with the protocol and follow-up visits. No formal interim analyses are planned. The baseline characteristics of those who did and did not drop-out will be compared to determine whether and how they differ. All tests and reported p-values will be two-sided. Estimates will be presented with 95 % confidence intervals.

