### Sample size

Sample size calculations were performed to detect a mean difference of ten minutes of MVPA between the intervention and control groups. In order to detect a difference of 10 min/day between groups, assuming a standard deviation of 18 min in MVPA [31], a power of 90 %, a significance of 0.05, a cluster size of 56 girls and an intra-class correlation of 0.1, the sample size needed is 18 schools, increasing to 20 schools (10 schools per group) to allow for cluster attrition. To allow for 30 % loss to follow up and non-compliance with the accelerometer we will recruit 80 girls per cluster (1600 girls in total).

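### The Statistical analysis section states two incompatible missing-data rules, so complete case as the primary analysis has to be inferred

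*Protocol article*

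**What the plan says.** All the statements on missing data in the analysis stand in one paragraph, the protocol article's Statistical analysis section. In order:

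- Ahead of any named analysis: "Data will be analysed on a complete case basis".
- For 14-month MVPA: "This will be examined using a linear multilevel model with MVPA as the outcome variable". The model has a school level, a term for randomised group and terms for the stratification factors. Baseline MVPA is not listed.
- After the secondary, mediation and subgroup analyses: "Missing data will be replaced using multiple imputation methods". The sentence is not tied to any analysis, outcome or covariate.
- Next: "As a sensitivity analysis, we will repeat the analysis on both an intention to treat basis and per-protocol basis".
- Then: "To allow intention-to-treat analyses, missing data will be imputed using multiple imputation methods".

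The Sample size section gives the scale: "To allow for 30 % loss to follow up and non-compliance with the accelerometer we will recruit 80 girls per cluster".

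**The concern.** The first and third statements are both general, and neither is limited to a particular analysis. One leaves out girls without an outcome and the other fills their outcomes in. The imputation sentence directly follows the statement that the subgroup analyses use the main-analysis models, so it can be read as covering the main and subgroup analyses. It is hard to treat it as an early mention of the sensitivity analysis, because imputation for that purpose gets its own sentence two sentences later.

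If the conflict remains, a complete-case estimate and an imputed estimate of the primary effect can each claim support from the published plan, and the choice could be made after both are known. The primary outcome depends on girls wearing a device and being present at follow-up, so one cannot assume that missingness is unrelated to activity.

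**Working it through.** **1. The plan's own figures.** Inputs from the Sample size section: difference 10 min/day, SD 18 min, power 90%, significance 0.05 (two-sided, from Statistical analysis), 56 girls per school, intra-class correlation 0.1.

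- Individually randomised: 2 × [18 × (1.960 + 1.282) / 10]² = 68.09, rounded up to 69 per arm.
- Design effect: 1 + (56 − 1) × 0.1 = 6.5.
- Schools per arm: 69 × 6.5 / 56 = 8.009, so 9 per arm and 18 in all. This matches the plan. (Without rounding to 69 the result is 7.90; a t-test on school means gives 90.1% power at 9 per arm.)
- Recruitment: 56 / (1 − 0.30) = 80 girls per school; 20 × 80 = 1600. This also matches.

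The calculation therefore counts 56 analysed girls per school, which fits a complete-case primary analysis.

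**2. The two analysis sets, at the planning allowance and with all 20 schools retained.**

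| Rule | Girls analysed | Imputed outcomes |
|---|---|---|
| Complete case | 20 × 56 = 1120 | 0 |
| Multiple imputation | 1600 | 0.30 × 1600 = 480 |

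**3. Effect on power.** Normal approximation, 10 schools per arm, SE = 18 × √(2 × DE / (m × 10)).

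- m = 56: DE = 6.5, SE = 2.743, power = Φ(10/2.743 − 1.960) = 95.4%.
- m = 80, all outcomes observed, an upper limit for imputation: DE = 8.9, SE = 2.685, power = Φ(10/2.685 − 1.960) = 96.1%.

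The gain is at most 0.7 percentage points.

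**4. Possible bias of complete case without baseline MVPA.** In an arm with missing proportion p, let g be the mean MVPA of observed girls minus that of missing girls. The observed mean exceeds the full mean by p × g, so the bias in the arm difference is p₁g₁ − p₀g₀. The document gives no values for p by arm or for g; the following are assumptions.

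- Same loss and same gap in both arms: bias 0, even if the less active girls are the ones missing.
- Unequal loss (25% and 35%), same gap of 9 to 18 min/day: 0.10 × 9 to 0.10 × 18 = 0.9 to 1.8 min/day in size, or 9% to 18% of the 10-minute target. The upper gap is a full SD.
- Equal loss of 30%, gap differing between arms by 5 to 10 min/day: 0.30 × 5 to 0.30 × 10 = 1.5 to 3.0 min/day, or 15% to 30% of the target.

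These figures show how far complete case could be off. They do not measure the distance between the two competing analyses.

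**The case against.** The strongest reply is that the paragraph already implies one reading. The complete-case sentence introduces the primary analysis. The intention-to-treat analysis is called a sensitivity analysis, and imputation is what makes it possible. An imputed primary analysis would leave that sensitivity analysis largely repeating it. The 56 analysed girls per school point the same way, and the stray sentence may be a duplicate. This stands, and it rules out the stronger claim that the primary analysis cannot be determined at all. It does not remove the conflict, since the reader must set aside one plain sentence to reach that reading.

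A second reply also stands in part. If only outcomes are missing and the imputation uses only the variables in the analysis model, the two analyses aim at essentially the same estimate. They diverge when the imputation draws on further information, such as baseline or 7-month MVPA, or is mis-specified.

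A reader might infer that the imputation will ignore schools and give intervals that are too narrow. The document does not say so. It commits to multilevel models, and the detail of an imputation model is commonly left to the analysis plan.

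**Conclusion.** The point holds as a contradiction in current text that bears on the primary analysis. It is not a complaint about missing detail: two general rules are stated and they are incompatible. An analysis plan that chose either would depart from a published sentence.

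Its reach is up to 480 of 1600 girls. That rests on the 30% allowance, which is a planning figure and not a forecast, and on all 20 schools remaining. The consequence for power is negligible. The consequence for bias cannot be fixed from the document; the illustrations of 0.9 to 3.0 min/day rest on assumed loss rates and activity gaps.

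A reader might conclude that complete case is biased whenever missingness depends on activity. That goes too far: in the set-up above, bias needs loss that differs between arms or a gap that differs between arms. Nor does the conflict show that the primary analysis should become a repeated-measures model. That is a preference, and with baseline MVPA as a covariate such a model would still lose girls without a valid baseline unless those values were handled.

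**What to change.** Before outcome data are seen:

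1. Name one primary missing-data approach. For example: all girls with valid 14-month MVPA, analysed in the arm to which their school was randomised, in the multilevel model already stated.
2. Add baseline MVPA as a covariate. It is already collected and already used to define the active and non-active subgroups. Say how missing baseline values are handled so that no girl with an outcome is dropped. This makes the missing-at-random assumption more plausible and improves precision.
3. Delete the unqualified imputation sentence, or limit it to the intention-to-treat sensitivity analysis, with imputation consistent with the multilevel model.

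If the investigators instead want imputation as primary, they should say so and label complete case as the sensitivity analysis.

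The cost is a few sentences and a little programming for the covariate and its missing values. No new data are needed, and the numbers of schools and girls do not change.

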### Secondary objectives

2.To investigate whether ‘Girls Active’ results in changes to the following outcomes at 7 and 14 months after baseline assessment:Increases in objectively measured total volume of physical activity.An increase in the proportion of girls meeting MVPA guidelines (measured objectively).Increases in objectively measured MVPA.Reductions in time spent sedentary (measured objectively and self-reported).Reductions in measures of adiposity (body mass index percentile, percent body fat).Improvements in psychological factors that may mediate physical activity participation (attitudes to physical activity, enjoyment of physical activity, motivation and confidence to be active, activity-related social support, physical self-perceptions).3.To determine the cost-effectiveness of the ‘Girls Active’ intervention.

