### Randomisation

Randomisation will occur after baseline assessments and will be carried out by the Leicester Clinical Trials Unit. Randomisation will occur at the school level (stratified by school size and proportion of Black and Minority Ethnic (BME) pupils) to receive either the ‘Girls Active’ intervention or carry on with usual practice (1:1).

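### The primary and secondary models leave out the baseline value of the outcome; the test stays valid with its stated power, but precision and protection against chance imbalance are given up

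*Protocol article*

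**What the plan says.** The Statistical analysis section writes the primary model out term by term. The outcome is MVPA at 14 months, there are levels for pupils within schools, and the fixed part is "a binary indicator for randomisation group as the explanatory variable, and terms for the stratification factors as confounders". Under Randomisation, those factors are school size and the proportion of Black and Minority Ethnic pupils. For the rest, "Secondary outcomes, including those measured at other time-points, will be analysed using the same strategy".

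Baseline values exist and come before allocation: "Randomisation will occur after baseline assessments". In the analysis section, baseline MVPA is named only as the median cut for the active versus non-active subgroup. No change score and no baseline-adjusted sensitivity analysis is stated. The secondary objectives ask whether the intervention "results in changes to the following outcomes at 7 and 14 months after baseline assessment".

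The Sample size section uses a target difference of 10 min/day, "assuming a standard deviation of 18 min in MVPA", 90% power, and "a significance of 0.05, a cluster size of 56 girls and an intra-class correlation of 0.1". This gives 18 schools, raised to 20 (10 per arm) for cluster attrition, with 80 girls recruited per school to allow for 30% loss.

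**The concern.** With only 10 schools per arm, the arms can differ at baseline by chance. Stratifying on two school characteristics, neither of them MVPA, need not prevent this. If baseline MVPA predicts 14-month MVPA, part of any such difference passes into the effect estimate, and a model without baseline cannot remove it. The same model also leaves in the residual variance that a baseline measurement, already collected, would explain.

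There is a practical side as well. If an imbalance is seen once the data are in, the investigators must either report an estimate that they know is shifted or add the covariate afterwards, which looks like choosing the model by its result. Minutes of MVPA are also the effect measure in the primary cost-effectiveness analysis, so any shift could carry through to it.

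**Working it through.** **1. Reproduce the planned sample size.** The inputs are in the Sample size section; the test is two-sided ("All tests and reported p-values will be two-sided").

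- Individually randomised: n per arm = 2 × [18 × (1.960 + 1.282) / 10]² = 68.1, rounded up to 69.
- Design effect = 1 + (56 − 1) × 0.1 = 6.5.
- Schools per arm = 69 × 6.5 / 56 = 8.01, rounded up to 9, so 18 schools.
- Check with a noncentral t on 16 df: SE 2.89 min, power 90.1%.
- Girls per school: 80 × 0.7 = 56.

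The stated figures are reached with no baseline correlation, so the calculation matches an unadjusted model.

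**2. Variance components.** Between schools: 18² × 0.1 = 32.4. Within schools: 18² × 0.9 = 291.6. Variance of a school mean = 32.4 + 291.6/56 = 37.6. SE of the difference between arms = √(2 × 37.6 / k), which is 2.74 min for k = 10 schools per arm and 2.89 min for k = 9.

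**3. Chance baseline imbalance.** Assume the same SD and ICC at baseline. With 10 schools per arm and 56 girls each, the difference in mean baseline MVPA has SD 2.74 min and a 95% range of ±1.96 × 2.74 = ±5.4 min. The probability that it exceeds 3 min in either direction is about 27%; for 5 min it is about 7%. With 80 girls per school the SD is 2.68 min and the range ±5.3 min. None of this credits any balance gained from stratification.

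**4. What an imbalance does.** An imbalance d shifts the unadjusted estimate by about slope × d. For d = 5 min and an assumed slope of 0.5, that is 2.5 min against a target of 10.

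**5. What adjustment would gain.** The protocol gives no correlation between baseline and 14 months, so these values are assumptions. With correlation r_w at pupil level and r_b at school level:

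Variance = 2 × [32.4 × (1 − r_b²) + 291.6 × (1 − r_w²)/56] / k

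Power is for 10 min, with one degree of freedom charged for the covariate.

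| Pupil / school correlation | Variance reduction | SE, 20 schools | SE, 18 schools | Power, 18 schools |
|---|---|---|---|---|
| Unadjusted | – | 2.74 | 2.89 | 90.1% |
| 0.5 / 0 | 3.5% | 2.69 | 2.84 | 90.8% |
| 0.3 / 0.3 | 9% | 2.62 | 2.76 | 92.3% |
| 0.5 / 0.5 | 25% | 2.38 | 2.50 | 96.1% |
| 0.5 / 0.7 | 46% | 2.02 | 2.13 | 99.2% |

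The school-level correlation drives the result, because the between-school part of the variance (32.4) is far larger than the pupil part (291.6/56 = 5.2). If baseline predicted nothing at either level, the lost degree of freedom would take power from 90.1% to 89.8%.

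**6. A limit of this formula.** It lets baseline have its own slope at each level. One common slope gives the same result where the two correlations are equal, and a poorer one where they differ. At 0.5/0, a common slope of 0.5 would make the bracket 32.4 × 1.25 + 5.2 × 0.75 = 44.4, above the unadjusted 37.6. At 0.5/0.7 it would be 32.4 × (1 − 0.7 + 0.25) + 3.9 = 21.7, still a reduction of about 42%.

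**The case against.** The best defence is that nothing in the stated analysis is invalid. Randomisation makes the unadjusted comparison unbiased over repeated allocations, 9 schools per arm give the stated 90% power, and 10 per arm give about 93%. That stands.

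It is also fair that the size of the gain rests on a correlation the protocol does not give. At weak school-level correlation the gain is small, and imbalances near ±5 min are uncommon. That stands too, and is why a range is shown.

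A reader might infer more than the text supports, in four ways:

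- **That imbalance passes in full into the estimate.** It passes in proportion to the slope, and the stratification factors are already in the model.
- **That the trial is underpowered, or that a smaller effect should be the yardstick.** The only target in the protocol is 10 min/day, and for that the power is as stated.
- **That objectives worded as changes conflict with a follow-up comparison.** A randomised comparison at 7 or 14 months answers whether the intervention caused a change.
- **That the cost-utility analysis has the same defect.** No regression model for QALYs is given, and an article may leave that to the full plan.

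The defence that covariates are left to an unseen analysis plan is weak here. The article lists the adjustment terms, and baseline is not among them.

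**Conclusion.** The point holds as a forgone improvement, not as an error that invalidates the analysis; it should be fixed. The listed primary and secondary models omit a covariate that is measured before allocation and already collected. The stated test and its 90% power are sound.

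What is lost is conditional protection against a chance baseline difference (SD about 2.7 min) and between about 3% and 46% of the variance of the effect. The first figure assumes that SD 18 and ICC 0.1 hold at baseline and ignores stratification. The second rests on the assumed correlations and on a model that fits the baseline relation at each level.

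**What to change.** In the Statistical analysis section, state that:

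- the primary model includes baseline MVPA as a covariate;
- each secondary outcome model includes that outcome's own baseline value where it was measured;
- girls with a 14-month outcome but no valid baseline value stay in the analysis, under a rule fixed in advance;
- the present model, without baseline, is reported as a sensitivity analysis.

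Whether baseline enters with one slope or with separate school and pupil slopes can be left to the analysis plan, in view of the limit in step 6 of the working. The change is a few sentences, made before outcome data are seen by arm. It needs no new data, schools or girls, and costs about one school-level degree of freedom.

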### Objectively measured physical activity

Participants will wear the GENEActiv Original accelerometer (Activinsights Ltd, Kimbolton, UK) continuously (i.e., 24 h/day) for seven days on their non-dominant wrist. This device has been found to be a valid and reliable objective measure of physical activity in young people [33]. Participants will be provided with a £5 gift voucher on return of their accelerometer with at least four valid days of data. The following variables will be calculated from the accelerometer data:Mean minutes of MVPA (overall and weekday and weekend split)Mean total volume of activity per day (overall and weekday and weekend split)Proportion of girls meeting the MVPA guidelines of 60 min per dayMean minutes of sedentary behaviour (overall and weekday and weekend split)

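### Effect modification by baseline activity is tested only through a split at the sample median, although baseline MVPA is recorded in continuous minutes and would give a stronger interaction test

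*Protocol article*

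**What the plan says.** Under Statistical analysis, the protocol article states that "Sub-group analyses involving interaction and stratified analyses will be performed" for four factors: baseline activity, single- or mixed-sex school, ethnicity and area deprivation. Baseline activity is defined by "non-active vs. active participants (defined as below or above the median MVPA level at baseline".

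The article then says "These sub-group analyses will use the same models as the main analysis". The main analysis is a linear multilevel model with pupils nested in schools, containing "a binary indicator for randomisation group as the explanatory variable, and terms for the stratification factors as confounders". Neither sentence mentions a continuous baseline-MVPA term or a continuous interaction.

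The section on objectively measured physical activity shows that the finer information is collected. The first variable derived from the accelerometer is "Mean minutes of MVPA (overall and weekday and weekend split". The article states no power or precision target for any subgroup test.

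**The concern.** The modifier is measured on a continuous scale and then reduced to two categories before the interaction is tested. All girls below the median are treated as alike, and so are all those above it. Two girls just either side of the cut are placed in opposite groups, while a girl just below it is grouped with the least active girl in the sample.

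The cut also depends on which schools and girls enrol. An effect reported for the non-active half therefore refers to no fixed number of minutes and is hard to carry to another population.

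What is at stake is the power to see whether the programme's effect changes with starting activity. Subgroup interactions are usually weakly powered, and the part of the loss that comes from the split is avoidable.

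**Working it through.** **Inputs from the article (Sample size).** Target difference 10 min/day ("In order to detect a difference of 10 min/day between groups"); SD 18 min ("assuming a standard deviation of 18 min in MVPA"); 90% power; "a significance of 0.05", two-sided according to Statistical analysis; 56 analysed girls per school; ICC 0.1; 18 schools needed, 20 recruited.

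**Assumptions, not in the article.** The shape of the baseline MVPA distribution, the form of the interaction, no between-school variation in the slope on baseline MVPA, and an interaction estimated from within-school contrasts.

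**1. The article's own figure.**
- Girls per arm without clustering: 2 × [18 × (1.960 + 1.282) / 10]² = 68.09.
- Design effect: 1 + (56 − 1) × 0.1 = 6.5.
- Schools per arm: 68.09 × 6.5 / 56 = 7.90. Adding one per arm for the small number of clusters gives 8.90, so 9 per arm and 18 in total.
- The t-based power with 9 per arm is 0.901. The stated 18 schools reproduce. The article gives no corresponding figure for the interaction.

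**2. Information kept by a median split.** For a linear interaction, the efficiency of the split relative to the continuous modifier is the squared correlation between X and the indicator that X exceeds its median.
- For a normal X this is 2/π = 0.637, so the loss is 1 − 0.637 = 36.3%.
- The standard error, relative to the effect estimated, is 1/√0.637 = 1.25 times as large.
- The analysed girls number 18 × 56 = 1008; for this test they act like 1008 × 0.637 ≈ 642.

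**3. Other distributions, linear interaction.**

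| Baseline MVPA | Information lost |
|---|---|
| Uniform | 25% |
| Normal | 36% |
| Gamma, CV 0.3–0.8 | 38–47% |
| Lognormal, CV 0.3–0.8 | 41–58% |

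**4. Power, normal case.** The within-school SD is 18 × √0.9 = 17.08.
- Continuous: SE of the interaction per baseline SD = 17.08 × √(4/1008) = 1.076. For 80% power the interaction must be (1.960 + 0.842) × 1.076 = 3.01 min per SD.
- Split: SE of the difference between halves = 17.08 × √(4/252) = 2.151, with 1008/4 = 252 girls per cell. The same interaction implies a difference between halves of 3.01 × 2√(2/π) = 4.81 min.
- Power of the split: Φ(4.81/2.151 − 1.960) = 0.61.
- The same steps starting from 90% power give about 73%.
- With the split, the difference between halves detectable at 80% power is 2.80 × 2.151 ≈ 6.0 min/day, and at 90% power 3.24 × 2.151 ≈ 7.0 min/day.

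**5. Clustered simulation** (18 schools of 56, ICC 0.1, interaction of 3.2 min per baseline SD, 1,500 runs per row).

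| Scenario | Split | Continuous |
|---|---|---|
| Normal, linear, baseline–outcome correlation 0 | 0.66 | 0.84 |
| Lognormal (CV 0.45), linear, correlation 0 | 0.57 | 0.83 |
| Normal, effect steps at the median, correlation 0.3 | 0.86 | 0.68 |

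The first two rows show the same loss as the formula. The third shows the order reversing when the true effect is a step at the cut.

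**The case against.** The median split is a defensible choice. It is fixed in advance, gives balanced groups, is easy to report and rules out a threshold chosen after seeing the results. The article openly defines the labels as relative to the median, promises no power for any subgroup and treats the analysis as one of several. A supplementary continuous interaction could also sit in an analysis plan that is not shown. All of this stands, and it keeps the point minor. It does not remove it: the article fixes the dichotomy as the definition of the factor, and a prespecified continuous interaction guards against post-hoc thresholds equally well.

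The size of the loss is also conditional. It depends on an unstated distribution and on linearity, and a true step at the median would favour the split. That is right. However, nothing in the article argues for a step there; the only activity threshold it uses elsewhere is the 60-minute guideline.

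A reader might infer more than the document supports:
- *That baseline activity is the main modifier because the programme targets disengaged girls.* The article does not rank the four factors. It opens eligibility to all girls aged 11–14 and sets no objective for less active girls. Its remark about girls who are not already sporty describes the peer leaders.
- *That a third of the information on whether the programme works in less active girls is lost.* The 2/π figure applies to the interaction test. The effect in the less active half is estimated directly by the stratified analysis.
- *That girls near the cut differ by less than measurement error.* The article gives no measurement-error figure.
- *That conclusions will be drawn from separate subgroup p-values.* The article plans an interaction and names it alongside the stratified analyses; nothing says the latter will carry the claim.

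**Conclusion.** The concern holds in limited form. The stated test of whether the effect varies with baseline activity uses a cut at the sample median when continuous minutes are available. With a normal modifier and a linear interaction, this costs 36% of the information for that test and lowers 80% power to about 61%. Across the distributions examined, the loss runs from about 25% to about 58%. The conclusion rests on approximate linearity, and the step at the median was the one scenario examined in which the split did better. This is a minor matter of efficiency and interpretability in a secondary analysis. It is not an error or a contradiction, and it has no bearing on the primary comparison or the number of schools.

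**What to change.** Make the prespecified test for this factor the interaction between arm and continuous baseline MVPA in the same multilevel model, with the main effect of baseline MVPA included. Use a linear term, with a spline as a check on linearity. Report predicted treatment effects with confidence intervals at stated values, for example the 25th and 75th centiles with their minutes given. Keep the median-split estimates as a display.

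The cost is one added sentence, slightly more analysis work and a linearity assumption, which the spline checks. No additional data are needed, and none of the planned estimates is lost.
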